
## DIFFERENCES BETWEEN THE STUDIES

Studies conducted on programs based on the modified dot-probe task differ in several ways. A significant difference lies in the temporal scope of the program and the time frame in which participants used the program. Everything from a single training session (Amir, Weber, Beard, Bomyea & Taylor, 2008) to a day in two weeks (See et al., 2009) or two times a week for four weeks appeared (Amir, in press; Schmidt et al., 2009). Large differences also exist in in outcome measures including different forms of anxiety estimates, clinician estimates, results of social stress tasks, measures of attention bias, or a combination of these (Amir, in press; MacLeod et al., 2009). Furthermore, different types of stimuli (pictures or words) were used and the training environment varied from a laboratory environment to the home environment (MacLeod et al., 2009; See et al., 2009; Amir, in press). A few studies have also delivered attention modification programs on the Internet (MacLeod, 2007; See et al., 2009). Programs based on the modified dot-probe task have been studied both in clinical and non-clinical populations (Amir et al., 2009; MacLeod et al., 2009). In studies conducted within clinical populations, anxiety and depression were mainly investigated but studies have also been conducted in patients with eating disorders, alcohol abuse, drug abuse, and aggression problems (MacLeod et al., 2009). Despite such different study groups, differences in symptoms, and differences in methodologically, the results show a promising potential of attention training for therapeutic purposes (MacLeod et al., 2009). In summary, research on the impact of cognitive processes on various mental disorders is still in its infancy and all the evolving evidence does not necessarily prove a functional effect on symptoms of anxiety (MacLeod et al., 2009). Replication studies are needed. Studies in clinical populations can possibly contribute to the understanding of the elements of selective processing that are associated with different types of psychopathology.

## ATTENTION TRAINING

The participation in training programs intended to train attention has shown good results in previous studies (eg Amir, in press; Schmidt et al., 2009). The intended training program will be programmed in Flash to be administered over the Internet and will be identical in all important aspects to the training program used in previous studies (Amir, in press). The Amir and Schmidt's studies training program began with a short instruction and then you could start a training session, which consisted of 160 trials. As shown in the two figures below, each trial began with the display of a plus sign which was presented in the center of the screen for 500 ms. Its function was to prepare and focus participants' attention. Then two faces of the same individual appeared, one on top of the screen and one at the bottom. Each pair of stimuli showed one of two possible combinations of facial expressions, neutral-neutral or neutral-disgust. The faces of the latter combination could have two possible display modes (top or bottom of the screen). After the facial pairs were shown for 500 ms, a letter (E or F) was presented in the same location of one of faces on the screen (top or bottom). Participants were instructed to press the right arrow key if the letter that appeared was an E and the left arrow key if the letter was an F. The letter remained until a response was registered, then the next trial started with a new plus sign. Participants were instructed to work as fast as they could without sacrificing accuracy. Previous research has shown that the percentage of correct responses in this type of task is about 95% and that the time to register a response usually hovers around 600 ms after some practice (Amir, in press). The total training time for a session was about ten minutes. Each training session included a total of 160 trials, which consisted of various combinations of letters (E or F), positions (top or bottom), facial expressions (neutral or disgust) and subjects (four female and four male faces). The images were 210x158 pixels in size and appeared centered at 58 pixel spacing. Of the 160 trials, 128 (80%) consisted of neutral-disgust facial expressions and the letter replaced the neutral face in all of these cases (2 (disgust-face position: top or bottom) X 2 (letter: E or F) X 8 (individuals) X 4 (repeat)). Through this approach the participant's attention was continuously directed away from the negative stimulus, even if participants were not expressly asked to do so. This is because the letter position was predicted by the disgust-face position in 80% of the trials. The remaining 32 trials (20% of the total) consisted of the combination of neutral-neutral facial expressions and the letter positions were randomized in these cases.

[figure not shown]

## TRAINING - PLACEBO

The placebo program’s structure was identical to the attention training program, with the difference that the letter was presented with equal frequency in the location of neutral and disgust facial expressions in the trials that involved neutral-threat presentation. In a total of 128 such trials, the letter hence followed the neutral face in 64 trials (40%), and the face that signaled disgust in 64 trials (40%). The remaining 32 trials (20% of the total) also consisted of neutral-neutral facial expressions and the letter was presented randomly equally on top or at the bottom.

[figure not shown]

## STIMULI FOR THE MODIFICATION OF ATTENTION BIAS

The faces that appear in the program are selected from a standardized set of emotional facial expressions (Matsumoto & Ekman, 1989). From these, facial expressions of eight subjects (four men and four women) have been selected as threatening and neutral stimuli. Facial expressions that signal disgust have been selected as threatening stimuli as previous research has shown that it is associated with aversion and rejection, something this population is especially sensitive to (Pishyar et al., 2004; Amir, Najmi et al., In press). Research has also shown that individuals with social phobia have an attentional bias in relation to facial expressions that signal disgust and have difficulty shifting their attention away from such stimuli (ibid.). Finally, previous studies with the attention training program made use of these stimuli and produced a positive impact on both the aforementioned attention bias and on symptoms (Amir, in press; Schmidt et al., 2009). However, there are studies that used words instead of faces. The words have then been specific to the targeted problem. This has for example been realized in generalized anxiety disorder (GAD) with good results. It has not yet been tested in social phobia. Examples of negative words in social anxiety disorder are "judged" and "shy". They are displayed together with a neutral or positive word on the screen. The aim is that the computer program assists the participant in drawing attention away from the negative word and towards the positive word.

## Purpose

In two studies we want to examine the most effective ways to train attentional bias. That is, if the use of words, images or a combination of both affects the efficacy of attention trainings. Furthermore, we will vary the exposure time (about 400-600 ms). The purpose of the study is trying to replicate, or improve, the very good results of two previous studies (see Amir and Schmidt) where a majority of participants no longer had the diagnosis after a short training period. The main difference between our and previous U.S. studies is that we want to deliver the training program via the Internet so that participants can practice at home instead of getting to a clinic.

Research questions

The questions are: is it possible to reduce social anxiety by modifying attention with an internet based training program administered in the home? Does this treatment provide statistical and clinically significant improvements in individuals with social phobia? When does improvement occur? Finally, are treatment effects stable over time examined with follow-up assessment at 4, 12 and 24 months after training completion. The two different studies will provide answers to the necessary intensity and frequency of training exercises as well as to whether combinations of words and images are more beneficial.

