## COMPUTERIZED AND INTERNET-BASED TREATMENT

Advances in information technology and increased use of computers and the Internet have contributed to the recent emergence of computer and Internet-based treatment modalities (Ritterband, Gonder-Frederick, Cox, West & Borowitz, 2003). It has also influenced the way we look at psychological treatments, for example, on how important we consider the interpersonal interaction in these contexts (template, Day & Greende, 2003; Greene & Iverson, 2009; Carlbring & Andersson, 2006.). Online therapy is already a fact (Mallen, Day & Green, 2003) and several randomized controlled trials have investigated the outcome of online therapy for a variety of psychiatric disorders, including social phobia (Carlbring & Andersson, 2006; Greene & Iverson, 2009). The majority of the applied treatments administered over the Internet have been based on cognitive behavioral therapy because this specific format is well suited to this medium (Greene & Iverson, 2009). Most online therapies have taken the form of bibliotherapy or self-help treatment with minimal therapist contact via email or telephone (Carlbring & Andersson, 2006). In summary, results of randomised controlled studies demonstrated good treatment results, many of which are clearly comparable to traditional forms of treatment, although there is still a need for more research in this area (Greene & Iverson, 2009; Carlbring & Andersson, 2006). Treatment that focuses on the training of cognitive functions for various psychiatric conditions in the form of, for example, working memory training (Klingberg et al., 2005), and, in fewer studies, applying attention training (MacLeod, Soong, Rutherford & Campbell, 2007), has also begun to appear in computerized or Internet administered shape. The benefits of computerized and Internet-based treatments are many (Greene & Iverson, 2009; Carlbring & Andersson, 2006; Ritterband et al., 2003). A clear advantage is the cost effectiveness of this type of treatment. In a "stepped care" approach, Internet-based treatments make it possible to provide a significantly greater proportion of patients with evidence-based care. Internet-based interventions require less therapist contact (Greene & Iverson, 2009). In a stepped care approach, Internet-based treatment is proposed as a first step and, after an evaluation, other forms of treatment can be offered to those who have not benefitted (ibid.). Another advantage is the possibility to reach out to the wider community, both in terms of availability of psychological therapy in general and for groups that otherwise would not have sought help at all (Marks, Shaw, & Parkin, 1998). Individuals with social anxiety have been shown to be a group who rarely seek help for their problems. Individuals with social anxiety also increasingly use the Internet to search for information about their problems and their treatment, and could thus take advantage of such opportunities as Internet-based interventions (Erwin, Turk , Heimberg, Fresco & Hantula, 2003). Another benefit of computerized and Internet-based treatments is the possibility for patients to benefit from treatment quickly and at times of day when the traditional psychological treatment is often not available. The time and cost to update any treatment manual is also lower than when the material is distributed in forms of books or papers (Marks et al., 1998; Carlbring & Andersson, 2006). For a treatment to be considered clinically effective, client compliance and satisfaction with treatment are very important factors (Greene & Iverson, 2009). A study by Proudfoot and colleagues (2003) has shown that patients with anxiety and depression are largely satisfied with Internet-administered cognitive-behavioral therapy and that drop-out is low, even lower than in traditional treatment. Disadvantages of this forms of treatment are the difficulties of establishing a diagnosis and to identify those individuals with more severe forms of psychiatric problems such as suicide risk (Carlbring & Andersson, 2006). One way to handle this is to use rigorous screening procedures that offer the option to exclude patients who exhibit severe depressive or suicidal problems early in the process (ibid.). Given that these risks also may arise or worsen during the course of treatment they should also be monitored on a weekly basis, for example. There should also be established procedures for dealing with such situations when they arise, for example by having the opportunity to contact the primary care provider (Maheu, 2003; Carlbring & Andersson, 2006). Other disadvantages mentioned are the lacking opportunity and/or the willingness of patients to make use of Internet-based or computerized therapy (Carlbring & Andersson, 2006). Reports from the Central Statistical Office (2006) show that 76% of the Swedish population has access to a computer at home and that more than 70% of those between 16 and 64 years use the Internet. The use is greatest in younger cohorts (16-19 years) and lower in older age categories (Swedish Institute for Transport and Communications Analysis, SIKA, 2006). Furthermore, the security and privacy aspects and differences in the hardware and software are also noteworthy potential disadvantages in this type of treatment. Carlbring and Andersson (2006) argue, however, that the available technology makes it possible to maintain both safety and ethical standards in these respects.

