Applicants who meet the criteria will be randomized into two groups so that half will undergo an effective attention training (experimental group) and the other half may start a supposedly less effective attention training (control group).

Prior to the treatment all research participants fill in outcome questionnaires that include of the following: Social Interaction Anxiety Scale, Social Phobia Scale, Liebowitz Social Anxiety Scale, MADRS-S, STAI-S, STAI-T, and Quality of Life Inventory (see Appendix 5 ). All forms are internationally established and have been shown to have good psychometric properties. These questionnaires will be administered at all measurement occasions.

Via the Internet, participants will take part in an attention training program (see description above) lasting for 14 days of active treatment. During this period, the exercises will be done with an intensity of 10 minutes of exercise per day.

Outcome questionnaires are administered 24 hours after the last training session. Follow-up assessments are then conducted after 4 months, 12 months and 24 months to evaluate the long-term treatment effects, and to compare these with the short-term effects. Pre-, post-, and follow-up measurements will be made with internationally established forms (see above) and the result will be calculated and statistically analyzed and reported at the group level.

### Study 2

The study applies the same procedure as Study 1, but instead of 14 consecutive days of daily training the training period will be extended to 4 weeks of active treatment with only two training sessions a week.

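### The protocol asks when improvement occurs, but its outcome schedule cannot show timing within the training period of either study

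*Protocol*

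**What the plan says.** Under Purpose, the research questions in the Protocol include "When does improvement occur". A separate, final question follows: "are treatment effects stable over time examined with follow-up assessment at 4, 12 and 24 months after training completion". The protocol thus ties the long follow-ups to stability and names no measurement for timing.

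The measurement times are in the Procedure section, under Study 1:

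- Baseline: "Prior to the treatment all research participants fill in outcome questionnaires".
- End of training: "Outcome questionnaires are administered 24 hours after the last training session".
- Later: "Follow-up assessments are then conducted after 4 months, 12 months and 24 months to evaluate the long-term treatment effects", and also to set the long-term effects against the short-term ones.

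The section sums up the scheme: "Pre-, post-, and follow-up measurements will be made with internationally established forms". It also requires the whole questionnaire set each time outcomes are measured.

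Training in Study 1 is daily, "lasting for 14 days of active treatment". Study 2 follows the same procedure, with two sessions a week over 4 weeks. The Ethics section lets control participants take the active training once the 4-month follow-up is done.

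**The concern.** The timing question stands apart from the stability question, and the later follow-ups belong to stability. The natural reading is that the protocol wants to know how improvement unfolds while people train. That needs at least one outcome between the start and the end of training, and none is scheduled.

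At stake is one listed research question. If the trial runs as written, a reader of the results could not tell whether symptoms fell in the first few days, steadily, or only near the end. The gap cannot be repaired once participants have finished training. It is therefore a matter for the protocol, and a statistical analysis plan cannot resolve it.

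**Working it through.** The protocol states no figure for this point, so there is none to reproduce. The check is a count of assessments against the training period, followed by the question of what the resulting data can distinguish.

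**Inputs (Protocol, Procedure, Study 1 and Study 2; Ethics)**

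| | Study 1 | Study 2 |
|---|---|---|
| Training period | 14 days | 4 weeks = 28 days |
| Sessions | 14 (daily) | 4 × 2 = 8 |
| Outcome before training | 1 | 1 |
| Outcomes during training | 0 | 0 |
| Outcome a day after training | 1 | 1 |
| Follow-ups | 4, 12, 24 months | 4, 12, 24 months |

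**Width of the intervals in which change can be placed**

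- Baseline to end of training: about 14 days in Study 1 and about 28 days in Study 2. Both are approximate. Baseline is fixed only as some time before treatment, and the end measure comes a day after the final session.
- End of training to first follow-up: about 4 months.
- Between later follow-ups: 12 − 4 = 8 months, then 24 − 12 = 12 months.

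Controls may take the active training after the 4-month assessment. The randomised contrast therefore exists at two post-baseline points only: the day after training, and 4 months.

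**What two readings can distinguish**

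Let D be the mean change from baseline to the end of training in one arm of Study 1. Consider three courses, taking day 7 as the midpoint:

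| Course | Baseline | Day 7 (not measured) | End of training |
|---|---|---|---|
| Early | 0 | D | D |
| Gradual (linear) | 0 | D/2 | D |
| Late | 0 | 0 | D |

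The measured columns are 0 and D in every row, so the three courses give the same data. The same holds for the difference between arms. In Study 2 a linear course would pass through D/4, D/2 and 3D/4 at days 7, 14 and 21, and none of these is observed.

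**Could the training task supply the timing instead?**

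The program registers every response, but the protocol names no session-level outcome. By the description of the training program that is to be reproduced, the letter replaces the neutral face in all 128 neutral-disgust trials of an active session. Those trials contain no contrast from which to form a bias score. Response times would in any case not measure social anxiety.

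**After the fix**

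One interior point in Study 1 cuts the interval from about 14 to about 7 days. Three interior points in Study 2 cut it from about 28 to about 7 days. In the table above, day 7 alone separates the three courses.

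**The case against.** The strongest reply is that the question does not mention training. There are four post-baseline occasions, and the procedure says that long-term effects will be compared with short-term ones. On that reading the trial does answer the question, coarsely: improvement is there by the end of training, or it emerges later. This stands. A reader might infer that the question has no data at all, and the documents do not support that. What is missing is resolution within training.

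Two other stronger readings are tempting and also fail.

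- *A contradiction on weekly monitoring.* The background section on computerized and Internet-based treatment says of depression and suicide risk: "Given that these risks also may arise or worsen during the course of treatment they should also be monitored on a weekly basis". A reader might set this against a procedure with no in-training measurement. But the sentence belongs to a literature review of Internet treatment in general, and it goes on to mark weekly monitoring as an example. It is not a commitment of this trial, so the procedure contradicts nothing. It also concerns safety, not when social anxiety improves.
- *Damage to the comparison of schedules.* A reader might argue that, without in-training data, the 2-week and 4-week schedules cannot be compared. The protocol describes randomisation to active or control training within each study and none between studies. The schedules also differ in both duration and number of sessions (14 against 8). In-training measurements would not remove those differences, so the gap is not what limits that comparison.

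It may also be said that Appendix 5, which holds the questionnaires, is not shown. The measurement times, however, are fixed in the Study 1 text itself.

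**Conclusion.** The point holds in a limited form. In-training outcome assessments number 0 in both studies. Improvement can be placed only in an interval of about 14 days (Study 1) or about 28 days (Study 2), or in the roughly 4 months after training. Its course within training is not identifiable. Beyond 4 months the gaps are 8 and 12 months, and no randomised contrast is protected.

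This rests on two assumptions: that the times listed under Study 1 are the full outcome schedule, as its own summary indicates, and that the timing question is meant to cover the training period, as its separation from the stability question suggests.

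The consequence is confined to this question. The comparison of arms after training and at 4 months, the sample size and the stability question are untouched. It is a worthwhile, inexpensive improvement and not a flaw in the main comparison.

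**What to change.** In the Procedure section, add one short social-anxiety scale already in the battery, for example the Social Phobia Scale. Give it online, in both arms, and regardless of how many sessions have been completed:

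- Study 1: day 7.
- Study 2: days 7, 14 and 21.

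Count days from the first training day. The protocol does not say that training starts on the day of randomisation, so counting from randomisation could miss the middle of training. Exempt these occasions from the rule that the whole questionnaire set is given whenever outcomes are measured. State that the arm-by-time profile will be estimated within each study.

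The cost is one extra short form per participant in Study 1 and three in Study 2, on a website that participants already use. Repeated self-rating may itself affect scores. Both arms receive the same forms, so the burden and this exposure are equal between them.

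If the extra forms are not wanted, reword the research question so that it asks only about the scheduled time points: whether improvement is present at the end of training or appears by 4 months. That costs nothing.

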## Ethics

Research participants participate voluntarily in the study. Participants will be informed on the potential benefit of the computerized attention training. Moreover, participants will be informed that any improvement requires active engagement.

The following ethical risks have been identified: the first is that participants who need specialized medical investigations could be included. At the slightest suspicion of unclear etiology, participants will be asked to consult a doctor in the community. The other risk is that deeply depressed individuals are included. Suicidal individuals will be excluded. This is done through a combination of the self-rating version of the Montgomery Asberg Depression Rating Scale and a clinical interview by telephone.

The individuals that are excluded from the study may perceive it negatively. All individuals who are excluded, therefore, will get advice on how and where they can seek alternative treatment in the community, and in cases where it is deemed appropriate recommendations for appropriate self-help literature will be made. Participants will be randomly allocated to one of two study groups (attention training or control condition). Best scientific practice does not allow the participants themselves to select the group and the individuals who do not agree to this will not be included in the study. Which participants belong to which group is also unknown to the research staff and disclosed only after the end of treatment at 4-month follow-up. Participants who are randomly assigned to the control group can take part in the attention training program after follow-up at 4 months. An obvious disadvantage of those randomly assigned to the control group is that they are likely to have a less effective treatment. Previous studies have shown positive effects in the control group, but more modest than in the experimental group. For this reason, all participants will be offered the supposedly more effective treatment after 4 months. It should be added, however, that the effects of being in the control group seem significantly larger than the expected spontaneous improvement in the same population.

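### The protocol promises answers on training intensity and frequency from two studies between which nobody is randomised and whose schedules differ in frequency and duration together

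*Protocol*

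**What the plan says.** The Research questions under Purpose close with a firm claim: "The two different studies will provide answers to the necessary intensity and frequency of training exercises".

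Allocation is described twice, each time as active against control only. Under Procedure, Study 1: "Applicants who meet the criteria will be randomized into two groups so that half will undergo an effective attention training (experimental group". Under Ethics: "Participants will be randomly allocated to one of two study groups (attention training or control condition". The protocol does not say how a person enters Study 1 or Study 2. The Sample size section treats them as two subprojects of 150, with 75 per group in each.

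The schedules are given under Procedure. Study 1 trains daily, "lasting for 14 days of active treatment", and "the exercises will be done with an intensity of 10 minutes of exercise per day". For Study 2, "The study applies the same procedure as Study 1", except that "the training period will be extended to 4 weeks of active treatment with only two training sessions a week". In both studies the post-treatment questionnaires follow one day after the final session, with follow-up at 4, 12 and 24 months.

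**The concern.** Schedule is the only difference between the studies that the Procedure section states, so an answer about frequency or intensity has to come from setting one study against the other. That contrast was not randomised. The schedules also differ in more than one respect, so a difference between the studies would not show which respect produced it.

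At stake is one stated research question. A reader of the results could take a cross-study difference as evidence of how much or how often people need to train, which this design cannot show. Allocation cannot be repaired after enrolment, and no later analysis plan can supply it.

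**Working it through.** **1. What differs between the schedules.** Inputs are from Procedure, Study 1 and Study 2. The 160 trials per session come from the description of the earlier program that the new one is to match ("Each training session included a total of 160 trials"). The 10-minute session in Study 2 is assumed from the same-procedure statement.

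| | Study 1 | Study 2 |
|---|---|---|
| Sessions per week | 7 | 2 |
| Weeks | 2 | 4 |
| Total sessions | 7 × 2 = 14 | 2 × 4 = 8 |
| Minutes at 10 per session | 140 | 80 |
| Trials at 160 per session | 2240 | 1280 |
| Post-treatment assessment | about day 15 | about week 4 |

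Total sessions is the product of frequency and duration, so two features vary freely and the third follows. With only two schedules, they cannot be separated. Session length is not stated to change, so in the protocol's own sense of the word, intensity may not vary at all.

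**2. What randomisation protects.** Let E1 and E2 be the active-minus-control effects in the two studies.
- E1 and E2 are each randomised contrasts.
- In E1 − E2, each study's concurrent control on the same schedule removes the main effects of case mix, season, natural recovery and assessment time. What remains is effect modification: if the samples differ in something that changes how well training works, E1 − E2 carries that difference.
- A raw comparison of the two active arms has no such protection and is fully confounded with study.

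**3. The protocol's own sample size.** It gives 75 per group, 80% power and d about 0.80, and no alpha. Assuming two-sided 5%, n = 2 × ((1.960 + 0.842)/0.80)² = 24.5, so 25 per group. The protocol says that it went to 75 for the predictor analysis and gives no inputs for that, so 75 can be neither reproduced nor refuted. The stated reason is not a schedule comparison.

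**4. Precision of E1 − E2.** Four arms of 75, SD units, two-sided 5% assumed, no dropout:
- SE = √(4/75) = 0.231
- Detectable at 80% power = 2.802 × 0.231 = 0.65 SD
- Power is 14% for a true difference of 0.2, 25% for 0.3, 41% for 0.4 and 58% for 0.5.

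The questionnaires are also completed before treatment, so the analysis can adjust for baseline. The SE is then multiplied by √(1 − r²), where r is the baseline-outcome correlation. The protocol does not give r; 0.5 to 0.7 is assumed here.

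| r | SE | Detectable at 80% | Power at 0.4 |
|---|---|---|---|
| none used | 0.231 | 0.65 | 41% |
| 0.5 | 0.231 × 0.866 = 0.200 | 0.56 | 52% |
| 0.7 | 0.231 × 0.714 = 0.165 | 0.46 | 68% |

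A true difference of 0.4 is an illustration: one schedule at the earlier d = 0.80 and the other at half of that.

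**5. Direct contrast of two active arms of 75, if randomised.** 2.802 × √(2/75) = 0.46 SD, without baseline adjustment.

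**The case against.** The strongest reply is that the protocol names no cross-study test. On a narrower reading, each study asks only whether its own schedule beats a control on that schedule. Those comparisons are randomised, and the leading questions (whether home training reduces social anxiety, and whether the gain is statistically and clinically significant) rest on them. This stands, and it limits the seriousness of the point. It does not rescue the sentence: two separate results against control do not show which intensity or frequency is necessary, and success in one study with failure in the other would not in itself be evidence of a difference.

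A reader might infer more than the documents support:
- *That the samples came from different advertisements or seasons.* The protocol describes one recruitment route and a total of 300 recruits. It is silent on how people reach either study; it does not say that the routes differ.
- *That any cross-study difference could simply reflect season, case mix or time since baseline.* That holds for a raw comparison of active arms. For the difference between E1 and E2, only effect modification remains.
- *That assessment timing is a major flaw.* The gap of about two weeks matters mostly at the post-treatment assessment. It is small relative to the 4-month follow-up, which precedes the offer of active training to controls.
- *That three separate dose features are confounded.* Two are free.
- *That joint randomisation would settle the question.* It removes bias between studies. It does not raise the power for E1 − E2 or separate frequency from duration, and participants would still know their schedule.

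**Conclusion.** The point holds in a limited form. The protocol claims that the two studies will answer a question about intensity and frequency, and the design lacks the property needed for this. The cross-study comparison is non-randomised. Even without bias, it would compare two packages that differ in frequency, duration and total sessions.

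The comparison is also imprecise. The detectable difference in effects is about 0.65 SD unadjusted, or about 0.56 to 0.46 SD if r is 0.5 to 0.7. These figures assume two-sided 5%, 80% power, 75 analysed per arm and no dropout.

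It might be inferred that the trial's efficacy findings are compromised. They are not: active against control within each study is randomised and unaffected. Because the fault lies in one research question and rewording cures it, this should be fixed but is not a bar to the trial. Nothing here bears on which schedule is preferable.

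**What to change.** **Minimum change.** Reword the sentence under Research questions so that the cross-study comparison is an exploratory, non-randomised comparison of two training packages, with no claim about intensity or frequency separately. Report it as the difference between the two baseline-adjusted active-minus-control effects, with a confidence interval. Cost: wording only.

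**Preferable, if both studies can recruit concurrently.** Randomise the same 300 people once, 1:1:1:1, to schedule and arm (75 each). This removes the between-study bias and allows a randomised active-against-active contrast (detectable d about 0.46). Conclusions should still be worded as packages. Cost: one allocation list and concurrent recruitment, with the same participants, programs and schedules. The protocol does not show whether concurrent recruitment is feasible, given screening interviews by final-term students, so the sponsor would need to confirm it.
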